### Consent

Consent to participate will be obtained in a three- stage process. OMs will give every offender a copy of the Client Information Leaflet (CIL) to take away to read before the next appointment. At the next appointment, OMs will ask the client if they have read the leaflet and whether they have any questions. OMs will then establish verbal consent to confirm eligibility to take part, collect some basic demographic information and to be screened for an alcohol use disorder. Those who then are positive on the screening tool will have the study explained to them verbally by OMs and in writing (using the Client Information Leaflet). Written informed consent will be obtained by OMs. This will include permission to give the client's data and contact details to the research team, and provide the research team with access to the clients Police National Computer (PNC) and probation records, and to participate in follow up after 6 and 12 months. The research team will then contact the participant within two weeks to thank him/her for taking part in the study.

## Interventions

### Client information leaflet

OMs randomised to the control condition, participating staff will be trained to screen eligible clients for hazardous or harmful drinking. Clients who screen positive and provide consent to participate in the study will complete the baseline questionnaire and then will be provided with a client information leaflet (CIL) http://www.sips.iop.kcl.ac.uk. The CIL to be used in this trial will be the Department of Health's "How much is too much; Drinking and You" leaflet [30]. This information booklet contains useful information about alcohol and includes the Drinkline telephone number where the client can access further information including treatment options for alcohol problems. Details of local alcohol services will also be attached to the back cover of the CIL.

### Brief advice condition

OMs randomised to deliver Brief Advice, will be trained to screen eligible offenders for hazardous or harmful drinking. Offenders who screen positive and provide consent to participate in the study will complete the baseline questionnaire and will then receive up to five minutes of simple structured brief advice from trained OMs using the SIPS Brief Advice tool "Brief advice about alcohol risk" which has been developed for the purpose of the SIPS programme. It is based on the "How much is too much?" Simple Structured Advice intervention tool, developed as part of the UK version of the Drink-Less Brief Intervention programme [31] from a prototype used as part of a World Health Organisation collaborative study on alcohol screening and brief intervention [32]. Offenders in this condition will also receive a Client Information Leaflet (CIL) from the OM at the end of the brief advice.

### Brief lifestyle counselling

OMs randomised to deliver Brief Lifestyle Counseling, will be trained to screen eligible offenders for hazardous or harmful drinking. Offenders who screen positive and provide consent to participate in the study will complete the baseline questionnaire and will then receive up to five minutes of simple structured brief advice from trained OMS using the SIPS Brief Advice tool "Brief advice about alcohol risk". Offenders in this condition will also receive a Client Information Leaflet (CIL) at the end of the brief advice. OMs will also be trained to refer offenders to an AHW, by making an appointment usually the following day or as soon as possible after probation attendance. The AHW will be experienced in carrying out alcohol assessment and brief interventions. The AHW will deliver a 20 minute brief lifestyle counseling intervention to offenders who attend the appointment at the probation office, using the SIPS Brief Lifestyle Counselling (BLC) Tool which has been developed for the purpose of the SIPS programme. It is based on the "How much is too much?" Extended Brief Intervention tool developed as part of the UK version of the Drink-Less BI programme [31] from a prototype used as part of a World Health Organisation collaborative study on alcohol screening and brief intervention [32].

All intervention tools and protocols are available from the SIPS study website http://www.sips.iop.kcl.ac.uk.

### Training and support

All OMs participating in the trial will be trained to implement alcohol screening and brief intervention according to the trial protocol. The aim of the training is to provide some background information about alcohol related harm, to give an overview of the study protocol, to familiarise staff with the screening tools, structure and scoring procedures, and to inform staff about the procedure for implementing screening and brief intervention in their site. Given the cluster design of the trial, staff will only be introduced to the screening tool they have been randomly allocated to. The training is individualised according to the implementation procedure agreed with the local collaborator and senior colleagues in probation.

A substantial element of the training will involve the understanding and familiarisation of alcohol units to ensure that the OMs are fully aware of the alcohol content of different alcoholic drinks so they are fully able to complete the screening tools accurately. Moreover, as the screening tools refer to standard drinks rather than Units when assessing consumption, the training ensures that staff are aware that a standard drink is one Unit and that they are able to convert different drinks into the number of standard drinks. Visual representations of standard drinks as well as several examples of people's drinking patterns are used to allow trainees to practice calculating in the alcohol content of each drink and to add up the number of standard drinks consumed in order to identify positive cases.

### Training of staff to deliver brief advice

Participating staff selected to deliver brief advice in probation randomised to either the Brief Advice condition or the Brief Lifestyle Condition will receive a one hour training session on how to deliver five minutes of brief advice according to the protocol.

The aim of the training is to provide OMs with the skills necessary to effectively deliver brief advice about alcohol risk to offenders attending the probation office in which the work. The training was developed by the SIPS team to be delivered by an AHW. The AHWs the SIPS team are experienced practitioners in the field of alcohol interventions. They contributed to the development of the training package and have been fully trained to deliver the training to practitioners.

The standard training package is based on a PowerPoint presentation with scripts to standardise delivery. The training sessions will be adapted for use in the different experimental conditions in which BA is being delivered.

The session will be presented to small groups of OMs who are encouraged to interact with the trainer, ask questions and comment on the content. This will be followed by an interactive role play session in which the AHW demonstrates the intervention, and then each OM will have an opportunity to practice with a co-worker, observed by the trainer who will provide feedback and encouragement. Training sessions will be delivered to groups of 1-6 practitioners with 1-3 being the typical group size.

### Training of staff to deliver brief lifestyle counselling

AHWs will be recruited to deliver the BLC within the participating probation offices. Staff recruited will, as a minimum, possess; a relevant professional qualification, a diploma in drug and/or alcohol studies or equivalent, 5 years post-qualifying experience with a minimum 2 years in an alcohol or drug speciality, prior knowledge and understanding of psychological interventions including motivational interviewing.

All AHW's will receive formal training and supervision from the point of recruitment. Training will be based upon the previous work of Rollnick et al [33] in addition to experiences from an earlier trial of screening and brief interventions [34]. The training will comprise of four main elements; orientation to the relevant OM, taught workshops, tape recorded simulated consultations with trained actors and ongoing clinical supervision provided by experienced senior clinicians.

The simulated consultations will be recorded and rated by three independent clinical assessors. The AHW will be assessed for adherence to the BLC protocol in addition to their behaviour and skills using the Behaviour Change Counselling Index (BECCI) [35]. Assessors will submit BECCI ratings, comments and supervision points for each consultation. This information will support clinical supervision and training until the AHW reaches a required standard of practice agreed by an independent clinical assessor.

## Outcome Measures

Participating OMs will be surveyed before and after training in each condition of the study to assess attitudinal factors and factors influencing implementation of screening and brief intervention procedures.

Attitudes will be assessed via the shortened Alcohol and Alcohol Problems Perception Questionnaire (SAAPPQ) [36]. A list of all OMs that can deliver alcohol screening and brief intervention in each study site will be compiled. A self-administered SAAPPQ will be distributed to participating staff on three occasions: pre- and post-training and post-study. SAAPPQ has five subscales covering role adequacy, role legitimacy, self-esteem, motivation, and work satisfaction. Role adequacy and role legitimacy are concerned with role security, i.e., how individuals perceive the adequacy of their skills and knowledge in relation to problem drinkers and how appropriate it is for them to work with such offenders. The subscales relating to self esteem, motivation and work satisfaction, are concerned with worker's therapeutic commitment, i.e., the extent to which they seek to engage drinkers in treatment and the extent that they find the work rewarding on both a professional or personal level [37].

In addition to the SAAPPQ, the post-training and post-study questionnaires will contain a number of semi-structured and open questions developed to elicit information on staff attitudes towards alcohol screening and brief intervention; previous experience of delivering alcohol screening and brief intervention; readiness to undertake these activities; the training needed to conduct screening and brief intervention; the suitability of each site to provide SBI; and potential barriers to effective implementation.

Factors relevant to implementation of screening and brief intervention have been found to be divided into *predisposing*, *enabling *and *reinforcing *factors [38]. Predisposing factors relate to Offender Managers' willingness to implement screening and brief intervention. Enabling factors are the skills and resources needed to implement screening and brief intervention. Reinforcing factors are visible results, feedback from peers and patients and other factors that encourage continuation of screening and brief intervention.

In this study we will modify the above [37] to survey Offender Managers before and after training and compare the above factors between different implementation models.

### System measures

The research team will identify the total number of offenders aged over 18 years who attended appointments with the Offender Managers in the trial during the recruitment period, the total number of offenders screened, the number screening positive and the number receiving an alcohol intervention in each of the 3 implementation models. This will allow calculation of the overall screening rate, the screen conversion rate (proportion of positive screens) and the intervention rate in the different settings. We will also compare these measures and the FAST versus M-SASQ screening tools.

Offenders' re-attendances at probation offices over the 6 and 12 month follow-up periods will be assessed using computerised records and compared with attendances by participating offenders in the 6 and 12 months before entry into the study. The sustainability of the screening and intervention approaches will be assessed by examining the extent to which screening and intervention activity continues after the end of the formal study recruitment period.

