## Objectives

The objectives of the trial are:

• To conduct a pragmatic multicentre cluster randomised controlled trial of screening and brief intervention for hazardous and harmful drinkers in typical probation settings in three English regions.

• To identify the most efficient methods for alcohol screening in typical probation settings.

• To compare the effectiveness and cost effectiveness of different models of brief intervention with an information leaflet in offenders with hazardous, harmful and dependent alcohol consumption.

• To assess the implementation of different screening and brief intervention approaches by Offender Managers (OMs) in typical probation practice.

• To identify attitudinal, practical, skill, resource, and reinforcing factors that predict successful implementation of screening and brief intervention in probation settings.

• To assess the relative impact of the different models of screening and brief intervention on uptake of alcohol services, including an alcohol helpline.

• To assess the relative impact of the three intervention strategies on reoffending.

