### Screening

In order to test the relative effectiveness of different screening methods in identifying hazardous and harmful drinkers we intend to conduct a cluster randomised comparison of two validated screening tools. A modified version of the M-SASQ which asks "How often do you have X or more standard drinks on one occasion?" where X = 6 for women and 8 for men, with monthly, or weekly, or daily or almost daily considered a positive screen [29]. We tested the M-SASQ in a pilot study and established a sensitivity of 91.8 and specificity of 70.8 when compared to the gold standard Alcohol Use Disorders Identification Test (AUDIT) [27]. FAST [28] is a universal screening tool that has high sensitivity and specificity in health settings ([28]. All screening tools have been modified to include a visual guide to interpreting a 'standard drink'. (A standard drink = 8 mg of pure ethanol = 1 UK Unit of alcohol).

All offenders who are attending probation and potentially eligible will be informed of the study and asked to consent to be screened. They will be screened using the instrument available to the OM. Participants will be informed of the outcome of the screening.

In all conditions, the research team will support participating OMs in implementing screening systems tailored to the needs of the probation office.

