### Client measures

#### Baseline

Immediately before receiving the initial CIL and/or brief advice intervention, participants will be invited by the Offender Manager to provide contact details and complete the Extended AUDIT [27], Euroqol (EQ-5D) [39], a short service use questionnaire (S-SUQ) [40] and modified Readiness Ruler [41]. Participants in the extended intervention will complete the baseline at the same stage as those in other groups.

AUDIT is normally used as a screening test for alcohol use disorders [27]. However in this context the AUDIT will be used as a means of establishing the severity of alcohol use disorders at baseline, in a way that is least intrusive to naturalistic aim of the trial in the probation setting and as a means of measuring the adequacy of matching between the intervention groups at baseline. The AUDIT contains 10 items to measure alcohol consumption, alcohol problems and dependence over, in this case, the previous 6 months, and the sum of the item scores provides a measure of severity which has been used in several previous studies, allowing comparability with other primary care samples [11]. We felt that the use of more elaborate baseline alcohol consumption measures would interfere with the naturalistic aims of the study and possibly would contribute a form of intervention in itself, so introducing bias into the evaluation of the interventions by reducing the difference between trial interventions. In addition, participants will complete the EQ-5D as a brief 5-item measure of quality of life [39]. Use of health, social criminal justice services and wider societal costs will be measured via a shortened version of Service Use Questionnaire [40] which allows estimation of health care and wider social costs for health economic analysis in the six months prior to intervention. A modified Readiness Ruler [41] containing a zero to ten scale of the extent to which participants think about their drinking as a problem or have addressed this issue will assess participants' motivational state regarding changing their drinking behaviour.

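### The measures named for comparing FAST with M-SASQ use no reference standard, so a difference in conversion rate cannot by itself show which tool identifies hazardous and harmful drinkers better

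*Protocol article*

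**What the plan says.** The Screening section says the two tools are put to a cluster randomised comparison in order to "test the relative effectiveness of different screening methods in identifying hazardous and harmful drinkers". The Aim also speaks of a tool to detect such drinkers, and adds efficiency and acceptability. The matching objective is "To identify the most efficient methods for alcohol screening in typical probation settings".

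System measures lists the counts to be collected (offenders attending, screened, screening positive, receiving an intervention) and the rates they yield: the overall screening rate, "the screen conversion rate (proportion of positive screens) and the intervention rate in the different settings". It continues: "We will also compare these measures and the FAST versus M-SASQ screening tools". The sentence is loosely worded, but its natural reading is that the same rates will be compared between the tools.

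On accuracy, the Screening section reports that the M-SASQ pilot "established a sensitivity of 91.8 and specificity of 70.8 when compared to the gold standard Alcohol Use Disorders Identification Test (AUDIT". For FAST it claims high sensitivity and specificity in health settings and gives no figure.

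The AUDIT is completed at baseline, after a positive screen and written consent. The Baseline section gives its purpose in this trial as measuring severity and checking that the intervention groups are comparable. No AUDIT is planned for clients who screen negative.

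**The concern.** Identifying hazardous and harmful drinkers is a question about correct classification. Of the three named rates, the screening rate measures uptake by Offender Managers. The conversion rate counts everyone who screens positive, rightly or wrongly. The intervention rate has no stated denominator: per client screened or attending it would also rise with false positives, while per screen-positive client it would say nothing about accuracy.

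The article calls the AUDIT the gold standard and collects it in consenting screen-positives, but states no use for it in the tool comparison. If the two tools convert at different rates, the named measures cannot tell a reader whether the tool with the higher rate found more drinkers or labelled more non-cases. At stake is the answer to the screening objective. The primary outcome and its analysis are not affected.

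**Working it through.** The article gives no figure for the tool comparison that could be reproduced. The check is whether the conversion rate can rank tools by accuracy.

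**Inputs from the article (Screening section).** M-SASQ sensitivity Se = 0.918 and specificity Sp = 0.708, both against the AUDIT in the pilot.

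**Assumed inputs.** True prevalence p of AUDIT-positive status among those screened: 30%, 50% and 70%. Comparator accuracy: first Se 0.918 with Sp 0.90, then Se 0.95 with Sp 0.85. The article supplies none of these, and they are not estimates for FAST.

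**Formulas.**
- Conversion rate = Se × p + (1 − Sp) × (1 − p)
- PPV = Se × p / conversion rate

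**Step 1, false positives for M-SASQ.** 1 − 0.708 = 0.292, so 29.2% of AUDIT-negatives screen positive. At p = 0.5, conversion is 0.459 + 0.146 = 0.605. Of 60.5 positives per 100 screened, 14.6 are false, about 24%.

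**Step 2, comparator with equal sensitivity and 90% specificity.**

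| p | M-SASQ conversion | Comparator conversion | Gap (points) | M-SASQ PPV | Comparator PPV |
|---|---|---|---|---|---|
| 30% | 0.2754 + 0.2044 = 48.0% | 0.2754 + 0.0700 = 34.5% | 13.4 | 57.4% | 79.7% |
| 50% | 0.4590 + 0.1460 = 60.5% | 0.4590 + 0.0500 = 50.9% | 9.6 | 75.9% | 90.2% |
| 70% | 0.6426 + 0.0876 = 73.0% | 0.6426 + 0.0300 = 67.3% | 5.8 | 88.0% | 95.5% |

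With equal sensitivity the gap is (0.292 − 0.100) × (1 − p) = 0.192 × (1 − p), which is false positives and nothing else.

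**Step 3, comparator better on both counts (Se 0.95, Sp 0.85).** Its conversion is 39.0%, 55.0% and 71.0% at the same three prevalences, against 48.0%, 60.5% and 73.0% for M-SASQ. The more accurate tool converts less each time. The gap shrinks as prevalence rises: at 80% the rates are 79.0% and 79.3%.

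**Step 4, what a difference contains.** In general, M-SASQ conversion minus comparator conversion is (0.918 − Se) × p + (Sp − 0.708) × (1 − p), where Se and Sp belong to the comparator. The first term is true cases gained or lost and the second is extra false positives. Randomising Offender Managers makes the expected p similar under both tools, apart from any selection in whom they screen. It does not separate the two terms.

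**The case against.** The strongest reply is that the article commits to no wrong inference. It says the rates will be calculated and compared, never that a higher conversion rate marks the better tool. Conversion is one of three rates, and alongside the numbers attending, screened and given an intervention it is an ordinary process description. The Aim and Objectives stress efficiency and acceptability, for which uptake is relevant. The tool also enters the analysis as a factor in the factorial design and in the multi-level models. Nothing bars the AUDIT from further use, and the full protocol or analysis plan may provide for it.

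Much of this stands. A reader might infer that the trial will name the less accurate tool as the better one, or that M-SASQ will be favoured. The article supports neither: it has no decision rule, no numeric accuracy for FAST and no prevalence. A reader might also infer that any excess in M-SASQ conversion would be wholly false positives. That follows only if the sensitivities are equal; if FAST were less sensitive, part of the excess would be true cases. Nor can it be said that the intervention rate rises with false positives, because its denominator is not given.

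What the reply does not meet is the mismatch within the article. The stated purpose is identification, and the measures named for it cannot separate cases from non-cases. Using screening tool as a factor in models of drinking outcome does not supply that separation. The point concerns measures the article chose and named, so it is more than a request for omitted detail.

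**Conclusion.** The point holds in limited form. The three rates named for FAST versus M-SASQ use no reference standard, and the conversion rate mixes true with false positives, so a difference in it does not by itself show which tool identifies drinkers better. The only size that rests on the article's own figures is the 29.2% of AUDIT-negatives expected to screen positive on M-SASQ, if the pilot specificity carries over to the trial.

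The gap of roughly 13 to 6 points in conversion, with PPV running the other way, is an illustration that depends on the assumed comparator and prevalences. It shows that conversion and accuracy can rank tools in opposite order, not that they will do so here. This is a cheap improvement to a secondary objective rather than a demonstrated error in a planned conclusion.

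**What to change.** Keep the screening, conversion and intervention rates as process measures, and state the denominator of the intervention rate. Add two measures by randomised tool, with Offender Manager as the cluster:

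- **PPV:** the proportion AUDIT-positive among screen-positive clients with a baseline AUDIT.
- **Yield:** AUDIT-confirmed cases per offender screened and per offender attending, with numerator and denominators covering the same period.

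The two belong together, because PPV alone would favour a strict tool that misses cases. Fix in advance the AUDIT cut-off that counts as positive, which the article does not give. Report consent and AUDIT completion by tool beside these measures. State that a conversion-rate difference alone will not be interpreted as better case identification, and that sensitivity and specificity cannot be compared because screen-negatives have no AUDIT.

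The cost is a little more analysis of data already planned, with no added burden on clients. The limitation is that both measures cover consenting positives only. Yield therefore also reflects consent and, per offender attending, screening uptake, so it does not isolate accuracy.
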